## Abstract

**Background:**

Chronic fatigue syndrome, also known as myalgic encephalomyelitis (CFS/ME), is characterized by chronic disabling fatigue and other symptoms, which are not explained by an alternative diagnosis. Previous trials have suggested that graded exercise therapy (GET) is an effective and safe treatment. GET itself is therapist-intensive with limited availability.

**Objective:**

While guided self-help based on cognitive behavior therapy appears helpful to patients, Guided graded Exercise Self-help (GES) is yet to be tested.

**Methods:**

This pragmatic randomized controlled trial is set within 2 specialist CFS/ME services in the South of England. Adults attending secondary care clinics with National Institute for Health and Clinical Excellence (NICE)-defined CFS/ME (N=218) will be randomly allocated to specialist medical care (SMC) or SMC plus GES while on a waiting list for therapist-delivered rehabilitation. GES will consist of a structured booklet describing a 6-step graded exercise program, supported by up to 4 face-to-face/telephone/Skype™ consultations with a GES-trained physiotherapist (no more than 90 minutes in total) over 8 weeks. The primary outcomes at 12-weeks after randomization will be physical function (SF-36 physical functioning subscale) and fatigue (Chalder Fatigue Questionnaire). Secondary outcomes will include healthcare costs, adverse outcomes, and self-rated global impression change scores. We will follow up all participants until 1 year after randomization. We will also undertake qualitative interviews of a sample of participants who received GES, looking at perceptions and experiences of those who improved and worsened.

**Results:**

The project was funded in 2011 and enrolment was completed in December 2014, with follow-up completed in March 2016. Data analysis is currently underway and the first results are expected to be submitted soon.

**Conclusions:**

This study will indicate whether adding GES to SMC will benefit patients who often spend many months waiting for rehabilitative therapy with little or no improvement being made during that time. The study will indicate whether this type of guided self-management is cost-effective and safe. If this trial shows GES to be acceptable, safe, and comparatively effective, the GES booklet could be made available on the Internet as a practitioner and therapist resource for clinics to recommend, with the caveat that patients also be supported with guidance from a trained physiotherapist. The pragmatic approach in this trial means that GES findings will be generalizable to usual National Health Service (NHS) practice.

**Trial Registration:**

International Standard Randomized Controlled Trial Number (ISRTCTN): 22975026; http://www.isrctn.com/ISRCTN22975026 (Archived by WebCite at http://www.webcitation.org/6gBK00CUX)

## Introduction

### Background

Chronic fatigue syndrome, also known as myalgic encephalomyelitis (CFS/ME), is a condition characterized by chronic disabling fatigue, which is not better explained by an alternative diagnosis [1-3]. The prevalence of CFS/ME in the population is between 0.4 and 2.5% [3-5]. A working group, reporting to the Chief Medical Officer for England, concluded the following: "CFS/ME is a relatively common clinical condition, which can cause profound, often prolonged, illness and disability, and can have a substantial impact on the individual and the family" [4]. The prognosis is poor with a median of 7% recovering without treatment [6].

The National Institute for Health and Clinical Excellence (NICE) guidelines recommend that patients with CFS/ME are offered GET (or cognitive behavior therapy [CBT]) [7]. In support of this guidance, two systematic reviews showed no harm to patients from GET [8,9]; however, it was concluded that larger trials should be completed to confirm the recommendations. The PACE trial (pacing, graded activity, and cognitive behavior therapy: a randomized evaluation) is the largest ever trial testing GET and CBT for CFS with 641 secondary care patients recruited [10]. Specialist medical care (SMC) alone was compared with SMC plus one of three therapies (adaptive pacing therapy, CBT, or GET). GET was found to be an effective and safe treatment, with 82% being satisfied with GET [11]. In contrast to this research, surveys of ME charity members have suggested that GET is perceived as a harmful and unacceptable treatment. In a recent survey, 56% of those who had received GET reported feeling “worse” afterwards, with 53% reporting GET to be unacceptable [12]. Specialist therapist-delivered GET is also intensive and expensive, with up to 15 sessions required over a 3 to 6-month period [9,11], and United Kingdom (UK) National Health Service (NHS) access is often poor and with long waiting lists [13]. An effective and safe guided self-help GET approach would be helpful to all involved.

Self-help approaches can benefit patients with chronic fatigue in the community [14]. In one study, fatigued patients attending their GP were given an educational CBT self-help booklet [15], complemented by 15 minutes of advice from a research nurse. After 3 months, patients who received the booklet were significantly less fatigued than the usual care group. This booklet has since been used in another primary care trial in which fatigued patients were offered 6 sessions of therapy with a trained GET or CBT therapist at their GP surgery or given the booklet without guidance as an alternative to usual care [16]. A third of patients receiving the booklet significantly improved compared to half receiving the face-to-face therapies.

However, these two studies recruited patients from primary care, and thus included those with less disabling fatigue than that found in secondary care patients. In another study, a guided CBT self-help treatment was tested in secondary care patients with CFS/ME [17]. In this trial, significant decreases in both fatigue and disability were observed in the guided self-help group compared to the waiting list control. A clinically significant improvement in fatigue (27% versus 7% of waiting list patients) and 6-point difference in mean SF-36 physical functioning subscale scores between groups at follow-up resulted. However, problems with respect to engagement and acceptability of psychotherapeutic approaches such as CBT for patients with CFS/ME have been reported [4].

Self-management techniques have consistently been shown to result in substantial improvements in patients with a range of mental illnesses [18-21] and physical illnesses [22,23]. A US study showed that patients with CFS/ME seemed to prefer self-management approaches, particularly social support services [24]. However, no study has investigated guided GET self-help for CFS/ME. In the UK, patients report difficulties accessing specialist services either because there is no local service, because of long waits for referral and/or subsequent treatment, or because they are too ill to travel to the clinic [25]. Approximately 40% reported waiting 6 months to see a specialist. Thus, effective guided self-help could open up a more accessible treatment option for many CFS patients and might make face-to-face therapy either unnecessary, or reduce the need for a full course of therapy.

### Rationale and Piloting

Physiotherapists trained to deliver GET within the PACE trial developed and tested the GES guide. It was developed so that diagnosed patients attending clinics could help themselves using such an approach with advice from their specialist clinician and therapist. The booklet was extensively piloted by secondary care CFS/ME patients and reviewed by several specialists in CFS/ME and a professor of physiotherapy. This led to significant revisions, and review, before “translation” of the guide into lay language by a professional editor.

### Hypotheses

First, we will test the null hypothesis that GES plus specialist medical care (SMC) will be no more effective at improving either physical disability or fatigue than usual SMC alone, as shown by no statistically significant difference between the two arms of the trial 12 weeks after randomization. Second, we will test the hypothesis that GES will be acceptable to patients diagnosed as having CFS/ME in specialist secondary care clinics, as demonstrated by less than 25% of eligible patients declining participation in the trial, and more than 75% of those participating being satisfied with the approach. Third, we will assess the difference in the number of participants suffering serious adverse effects, serious adverse reactions, or a serious deterioration across the study arms.

We will also assess whether there is a statistically significant difference in cost-effectiveness between the two interventions, although this is not a hypothesis.

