### Interventions

#### Standard Medical Care (SMC)

Participants will be informed at the end of their assessment appointment that they have been allocated to SMC and that they should follow the advice of their GP and specialist doctor as usual. They will not have access to the self-help booklet used in the trial. As per usual, specialist doctors will prescribe or advise regarding medication as indicated for symptomatic treatment of associated symptoms (eg, insomnia and pain) and comorbid conditions (eg, depressive illness). These patients will start the therapy to which they have been referred after the endpoint of the trial at 12 weeks or more after randomization, when it becomes available. After completion of trial participation, these patients will also receive a copy of the GES booklet.

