#### 12-Weeks Post-randomization

The main outcome end-point will be 12 weeks after randomization, before patients begin their service therapy. We chose 12 weeks as this was about the length of the waiting list for therapy at the St Bartholomew’s CFS service at the time of application for funding. At the end-point, the following information will be collected via questionnaires sent by mail with a stamped addressed envelope: SF-36 PF, CFQ, self-rated Clinical Global Impression of Change (CGI) [39] (this will be done once for overall health and then a second time specifically for CFS), HADS, EQ-5D, WSAS, IPAQ, CSRI, and PHQ-15. Participants will be asked to describe the following: whether they have used any of 4 listed self-help resources since randomization, including the unpublished GES guide [40-42]; how satisfied they are with the help they received; how closely they followed the GES guide; their current employment status and whether they have had to reduce/stop work due to their CFS/ME; any new health problems not already reported; and whether they are taking antidepressant medication for any reason.

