#### Non-Responders

If a returned form is incomplete, the researcher will contact the patient, usually by telephone, to acquire any missing data. In the event that no outcome data is completed or returned after 2 telephone attempts spaced 1 week apart, the researcher will email or text the participant to ask for answers over the telephone or via email solely for the 2 primary outcomes and the CGI. The researcher will make a file note that the outcome data were collected in this way. If a participant withdraws from the treatment, but not the trial, data will be collected in the usual way. If the participant is not willing to provide all follow-up data, a request will be made to complete only the primary outcome and CGI; if the participant agrees, these will be completed immediately.

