#### Sensitivity Analysis

Sensitivity analysis will be conducted to assess the impact of missing data on our results. We will estimate whole-scale missing data due to loss to follow-up using multiple imputation by chained equation. This will allow us to conduct a strict ITT for all respondents who took part at baseline. Following recent guidelines, we will also conduct a sensitivity analysis that will take into account the partially nested design of the study and, therefore, assess the potential impact of the “therapist effect” on our results [46]. Further analysis will be conducted to adjust for potential confounders, including sex and age.

A per-protocol analysis will serve as a further sensitivity analysis to investigate the robustness of the conclusions of the primary analysis, following departures from the randomized intervention policies. This will exclude those participants in the control arm who used a GET self-help approach. Subgroup analyses including only those meeting the Oxford or CDC criteria for CFS will also be undertaken. We will analyze moderators of improvement, such as these criteria, but also depression and severity of physical function and fatigue. These subgroup analyses are exploratory and will be interpreted with due caution [47].

#### Analysis for Hypotheses 2 and 3

Chi square will be used to describe any difference in satisfaction (ie, satisfied vs nonsatisfied) across treatment arms and any differences in SAEs, SARs, or serious deterioration (1+ vs none) across treatment arms.

The above plan is what we intend to do; however, the final analyses reported may differ from those planned, allowing for *post hoc* analysis where it is indicated [48]. We will report alternative methods if statistical models do not converge, and omit planned analyses that are superseded, redundant, or no longer of interest. We will report any changes in consequent papers.

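### Hypothesis 2 sets absolute acceptability criteria (under 25% declining, over 75% satisfied), but the one analysis named for it, a between-arm chi-square, tests neither, and the 75% denominator is not limited to the GES arm

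*Protocol article*

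**What the plan says.** Under Hypotheses, the second hypothesis is introduced as something to be tested: "Second, we will test the hypothesis that GES will be acceptable to patients diagnosed as having CFS/ME in specialist secondary care clinics". It has two criteria: "less than 25% of eligible patients declining participation in the trial, and more than 75% of those participating being satisfied with the approach".

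Under Analysis for Hypotheses 2 and 3, the only analysis that bears on this hypothesis is: "Chi square will be used to describe any difference in satisfaction (ie, satisfied vs nonsatisfied) across treatment arms". That section mentions neither the 75% nor the decline rate. Data Entry and Analysis plans a descriptive comparison of the characteristics of those who did and did not agree to take part, and a CONSORT flow diagram.

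Three other places affect what can be measured:
- 12-Weeks Post-randomization: all participants are asked "how satisfied they are with the help they received".
- Standard Medical Care (SMC), about the control arm: "They will not have access to the self-help booklet used in the trial".
- Non-Responders: after two failed telephone attempts, answers are sought "solely for the 2 primary outcomes and the CGI". Participants unwilling to give full follow-up data are likewise asked only for the primary outcome and the CGI.

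The Discussion makes release of the booklet depend on GES being acceptable, safe, and clinically useful relative to control.

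**The concern.** The hypothesis is an absolute statement about GES; the named analysis is a relative statement about two arms. A difference between arms does not show whether satisfaction with GES exceeds 75%, and similar arms do not show that it falls short. The decline criterion has no analysis at all. This is more than detail left to an analysis plan, because the article names an analysis for this hypothesis and that analysis answers a different question.

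The satisfaction denominator is also loosely fixed. It is given as those participating, directly after a phrase about participation in the trial, so the literal reading covers both arms. Half of those people never receive GES, and the question they answer concerns whatever help they had.

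At stake is one of the trial's three numbered hypotheses and one of the conditions for releasing the booklet. The Background reports a survey in which 53% of respondents who had received graded exercise therapy found it unacceptable, so readers will look closely at how acceptability was judged.

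**Working it through.** **Inputs.** Sample Size gives 98 per group analysed and 109 per group randomized (218 in total). These figures reproduce: a difference of 8, SD 18, two-sided alpha 2.5% and 80% power give 97.5, so 98, per group with the t-based solution, and 98/0.9 = 108.9, so 109. The thresholds of 25% and 75% have no calculation behind them in the article. All satisfaction counts below are hypothetical.

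**1. Does the chi-square track the 75% criterion?** For equal arms of n, z = (p1 − p2) / √[2p̄(1 − p̄)/n], without continuity correction.
- GES 59/98 (60.2%) v SMC 39/98 (39.8%): p̄ = 0.50, difference 0.204, SE = √(0.5/98) = 0.0714, z = 2.86, p = 0.004. The arms differ clearly, but GES is well below 75%.
- GES 83/98 (84.7%) v SMC 83/98: p = 1.00. There is no difference, but GES is above 75%.
- GES 83/98 v SMC 78/98 (79.6%): p = 0.35. Again GES is above 75%.

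The two questions can disagree in either direction.

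**2. The decline criterion.** Declining precedes allocation, so there are no arms to compare. If eligible patients are counted as randomized plus decliners (an assumption), (N − 218)/N < 0.25 requires N < 218/0.75 = 290.7. At N = 290 there are 72 decliners (24.8%, criterion met); at N = 291 there are 73 (25.1%, not met). The count could be read from the flow diagram, but no comparison with 25% is planned.

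**3. What the denominator could do.** With equal arms, a literal both-arm figure would be (GES% + SMC%)/2.
- GES 68%, SMC 85%: (68 + 85)/2 = 76.5%. Above 75%, although GES alone is below.
- GES 85%, SMC 60%: (85 + 60)/2 = 72.5%. Below 75%, although GES alone is above.

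These show only that the choice of reading can reverse the answer.

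**4. Precision.** The Wilson 95% interval is [p + z²/2n ± z√(p(1 − p)/n + z²/4n²)] / (1 + z²/n). For 74/98, p = 0.7551, z²/2n = 0.0196 and 1 + z²/n = 1.0392. The centre is 0.7747/1.0392 = 0.7455 and the half-width 1.96 × 0.0446/1.0392 = 0.0841, giving 66.1% to 83.0%. If the true rate were 72%, at least 74 of 98 (an observed figure above 75%) would still occur with probability 0.257.

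**5. Missing satisfaction.** The fallback contact does not collect satisfaction. If 74 were satisfied among 98 respondents and the other 11 of 109 randomized to GES were counted as not satisfied, the figure becomes 74/109 = 67.9% instead of 75.5%. That those 11 would be less satisfied is plausible but not documented, so this is a sensitivity analysis and not a correction.

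**The case against.** The best defence is that the criteria are descriptive: acceptability is to be shown by observed percentages, and comparing two percentages with two cut-offs needs no further test. The chi-square is built on the GES-arm proportion, the flow diagram gives the decline count, and interval methods and missing-data rules often sit in an analysis plan. This stands in part. The numbers can be recovered and no new data are needed, which lowers the severity. It does not remove the mismatch, because the article says the hypothesis will be tested and then names an analysis that does not bear on either criterion.

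Three stronger readings might be inferred, and the document does not support them.
- *The arms will be pooled for the 75% figure.* Nothing says so. Satisfaction is with the approach, which in that sentence points to GES, and the named analysis keeps the arms apart. The denominator is ambiguous, no more.
- *The chi-square p-value will decide acceptability.* No such rule appears. The test is there to describe a difference, and that is a reasonable additional question since both arms rate the help they had.
- *The lower confidence limit must exceed 75%.* The stated bar is a proportion above 75%. Requiring the lower limit to clear it would need 82/98 (83.7%; Wilson 75.1% to 89.7%), a stricter rule on which reasonable statisticians differ.

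Acceptability alone does not trigger release of the booklet either; safety and a clinically useful difference are also required.

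**Conclusion.** The point holds as a mismatch between a hypothesis and its named analysis, together with an ambiguous denominator. The between-arm chi-square can be significant with GES at 60% satisfied and null with GES at 85%, and it has no bearing on declining. Under the literal denominator, the SMC arm could move the figure across 75% either way. Near the threshold, the GES-arm estimate carries an interval of about 66% to 83%.

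These sizes rest on hypothetical satisfaction rates, 98 respondents per arm, and eligible patients counted as randomized plus decliners. The conclusion that neither criterion is tested does not depend on them. Severity is moderate to minor: the primary outcomes, sample size and efficacy conclusions are untouched.

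**What to change.** In Hypotheses, define the 75% criterion on participants randomized to GES.

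In Analysis for Hypotheses 2 and 3:
- Report the GES-arm satisfaction proportion with a 95% confidence interval (Wilson, for example) against 75%.
- Report the proportion of eligible patients who declined, with a 95% confidence interval, against 25%. Describe it as acceptability of the trial, since refusal may also reflect randomization and research burden.
- Add a sensitivity analysis that counts missing satisfaction as not satisfied, because the Non-Responders fallback omits that item.
- Keep the between-arm chi-square as a separate descriptive comparison.

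This needs changes of wording only, with no new data collection and no change to the sample size. As the article reports analysis already under way, the definition should be recorded before satisfaction by arm is examined, or else reported as a later clarification. The cost is that the acceptability claim will be shown with its imprecision.

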## Methods

### Study Design

This is a pragmatic [26] randomized controlled trial of outpatients attending two specialist CFS/ME secondary clinics who have been diagnosed by a specialist doctor as having CFS/ME and referred for practitioner-delivered therapy. All participants will be on a waiting list for therapist-delivered treatment. Standard medical care (SMC) will be compared with SMC plus GES.

### Participants

Adults aged 18 and over will be recruited after assessment at two CFS/ME specialist clinics in the United Kingdom (UK): one at St Bartholomew’s Hospital (East London Foundation NHS Trust) and the other in Kent (Kent and Medway NHS and Social Care Partnership Trust). These services each provide assessment and/or treatment for approximately 125 new adults each year, referred mainly from general practitioners. Adults are given a diagnosis after a clinical assessment, with a physical and mental state examination, and screening blood tests according to the guidelines produced by the National Institute for Health and Care Excellence [7]. Approximately 57% of adults referred to specialist CFS services have CFS/ME [27] based on one of three possible criteria [1,2,7]; however, they must meet NICE criteria to be entered into this trial. We chose the NICE criteria to maximize generalizability of the trial to a more representative sample of UK secondary care attendees, as they are more inclusive (requiring a shorter duration and fewer symptoms).

### Inclusion/Exclusion Criteria

Patients will be included if they meet NICE criteria for CFS/ME [7]. To meet these criteria, patients must have clinically evaluated, unexplained, persistent or relapsing chronic fatigue of more than 4 months with a definite onset. Their fatigue needs to have resulted in a substantial reduction in activity, be characterized by postexertional fatigue or malaise and be accompanied by at least 1 of 10 possible symptoms (eg, headaches, muscle and/or joint pain, difficulty sleeping, and concentration problems). Patients meeting these criteria will be referred for treatment in the service as usual and will be asked if they would be willing to be contacted about possible participation in the trial. Patients will not be offered trial participation if they do not speak and read English adequately, have current suicidal thoughts or comorbid psychiatric conditions requiring exclusion, have read the GES guide previously, have had previous GET therapy at one of the trial clinics, or have physical contraindications to exercise.

